## Abstract

**Introduction:**

Childhood stroke leads to long-term neurological impairment, impacts on quality of life and has substantial economic costs. Coordinated systems of care are required to streamline rapid diagnosis and treatment of stroke. The primary aim is to investigate the effect of Code Stroke protocols on increasing the proportion of children with stroke diagnosed within the 4.5-hour time window for reperfusion therapies.

**Methods and analysis:**

Prospective, multicentre, quasi-experimental interventional study in nine Australian and New Zealand children’s hospitals from 2020 to 2026. Children aged 1 month to <18 years with stroke symptoms are eligible for inclusion. A staged pre-implementation and post implementation study design will investigate effects of (1) Code Stroke protocols to streamline diagnosis and treatment, (2) decision support tools to improve diagnostic accuracy and (3) perfusion imaging to quantify brain at risk of infarction. Presenting characteristics, timelines of care, treatments, functional and health economic outcomes will be collected. The primary outcome is the proportion of children with stroke diagnosed within 4.5 hours, estimated using a mixed-effect logistic regression model, with the dichotomous variable time to diagnosis as the dependent variable, implementation phase as the independent fixed effect and hospitals as random effects. Sample size calculation estimates that 98 patients with radiologically confirmed stroke per phase will yield 80% power to detect change from 15% to 40% in the proportion of children diagnosed within 4.5 hours.

WHAT IS ALREADY KNOWN ON THIS TOPICReperfusion therapies including thrombolysis and clot retrieval, which save viable brain, have transformed health outcomes for adults with stroke. Children are not accessing reperfusion therapies because of delays to diagnosis.There are limited data reporting efficacy and safety of reperfusion therapies, and their impact on functional outcomes, because major trials have excluded patients younger than 18 years of age.

WHAT THIS STUDY ADDSThis will be the first multicentre, prospective study of acute childhood stroke care undertaken in Australia and New Zealand to improve the understanding of the impact of Code Stroke protocols on improving patient outcomes.This pragmatic, real-world study will provide new evidence for the effect of standardised clinical and diagnostic imaging protocols, advanced stroke imaging and decision support tools on the efficiency and effectiveness of stroke diagnosis and treatment practices.HOW THIS STUDY MIGHT AFFECT RESEARCH, PRACTICE OR POLICYThis study will provide best available data on the effect of interventions to identify children most likely to benefit from reperfusion therapies that can save viable brain.This study will have a bi-national impact in Australia and New Zealand and will be relevant for international efforts to improve systems of acute stroke care for children.The study will provide data on the impact of shortening time to diagnosis and increased access to reperfusion therapies on functional and health economic outcomes.

## Introduction

 Childhood stroke has a pooled incidence of 2.1 per 100 000 person-years.^1^ Global impact is growing, with a 35% increase in prevalence from 1990 to 2013.^2^ Childhood stroke is associated with high rates of neurological impairment and substantial economic costs.^3
4^ Stroke is eminently treatable but time-critical. Reperfusion therapies, which include intravenous thrombolysis and endovascular clot retrieval (ECR), are established as effective to improve long-term outcomes of adults with acute ischaemic stroke.^5
6^

The catchcry in emergency stroke treatment that *time is brain* is equally applicable to children because failure to save brain results in poorer outcomes.^7^ Survivors of childhood stroke face decades of living with disability and with that comes a significant impact on their families and the broader community. The long-term economic and societal cost of childhood stroke is not well elucidated, with previous US studies reporting the economic impact only up to 5 years from stroke event.^3^

The days of therapeutic nihilism in adult stroke have passed, yet children are still not receiving the benefits of reperfusion therapies, often because of diagnostic delay, sometimes extending beyond 24 hours.^8^ Delays prior to arrival relate to limited awareness of stroke among caregivers,^9^ clinical recognition among paramedics^10^ and emergency physicians,^11^ and poor accuracy and reliability of prehospital decision support tools.^12^ In contrast to adults, in-hospital factors—particularly delayed access to rapid diagnostic imaging in the emergency department (ED)^13^ and poor sensitivity of CT-based imaging for detection of infarction in children with arterial ischaemic stroke (AIS)^14^—are more important contributors to delayed diagnosis than prehospital factors. Therefore, institutional and regional systems of acute care are required to streamline diagnosis and initial treatment of childhood stroke.

In adults with stroke, there has been a move towards tissue-based rather than time-based selection of candidates for reperfusion therapies to salvage viable brain. This approach using advanced brain imaging, which quantifies penumbral tissue destined for infarction if blood-flow is not restored, has led to use of thrombolysis^15
16^ and ECR^17^ in extended time windows beyond 4.5 and 6 hours, respectively. These diagnostic advances have only recently been tested in observational studies in children^18
19^ and require further investigation to determine their utility to identify children most likely to benefit from treatment.

Data from an international registry suggests that thrombolysis is safe in children^20^ but efficacy for improving functional outcomes remains unclear, with the literature mainly confined to retrospective studies^21–26^ reporting outcomes at the time of discharge^21–23
25^ or in combination with ECR at 90 days.^21
24
26
27^ A recently established prospective international registry of 208 paediatric patients provides evidence for efficacy of ECR in children with large or medium vessel occlusion. Despite having more severe stroke symptoms, children treated with ECR had better functional outcomes observed at 90 days post-stroke when compared with those treated with best medical therapy (which included thrombolysis).^27^

Despite these limitations, there has been substantial progress over the past 10 years in the development of clinical practice guidelines^28
29^ and institutional paediatric stroke protocols to standardise the approach to acute recognition, diagnosis and emergency treatment of childhood stroke. Recent studies from France^30^ and Spain^31^ have demonstrated the benefits of developing regional hospital systems of acute care, with designation of hospital-based primary and comprehensive stroke centres. No studies, however, have adopted a coordinated national approach to acute stroke care, with protocols tailored to local resources.

### Objectives and hypotheses

The primary aim of the Australian Paediatric Acute Code Stroke (PACS) study is to investigate the effect of Code Stroke protocols on increasing the proportion of children aged 1 month to less than 18 years of age who are diagnosed within 4.5 hours of stroke symptom onset—as the time window for thrombolysis.

The secondary aims of the study are to (1) increase the proportion of children receiving reperfusion therapies, (2) investigate the feasibility and utility of automated perfusion software to guide clinical decision making, (3) test the utility of clinical decision support tools to improve accuracy of paramedic and ED physician diagnosis, (4) estimate the economic impacts of shorter time to diagnosis and access to reperfusion therapies and (5) benchmark functional outcomes at 3 months post-event against adults with stroke.

The main research questions are: do acute stroke protocols (1) decrease the time to diagnosis of childhood stroke and (2) increase access to reperfusion therapies that salvage viable brain?

We hypothesise that standardised institutional Code Stroke protocols, in combination with automated perfusion imaging and clinical decision support tools, will improve the efficiency (shorter time to diagnosis) and effectiveness (increased access to reperfusion therapies) of acute stroke care in children with stroke.

## Methods and analysis

### Study design

A quasi-experimental, two-tiered preintervention and postintervention study design will be used to evaluate the effects of the study interventions in tertiary children’s hospitals in Australia and New Zealand. The pre-implementation phase is the 3-year period from 2015 until 2017, reflecting the era prior to the launch of the Australian guideline for the acute management and diagnosis of stroke in children.^28^ The combined protocol development and post implementation phases are from 2018 to 2026. The study will follow the Transparent Reporting of Evaluations with Non-randomised Design statement for quasi-experimental non-randomised trials.^32^

### Patient and public involvement

A Steering Committee has been established to oversee governance of the study and reporting of progress, which is chaired by the Stroke Foundation (as the grant recipient and leading non-government stroke advocacy organisation in Australia). The committee has representation from Australian parents with lived experience of childhood stroke, to provide expert knowledge, advice and guidance, and to represent the interests and viewpoints of the Australian and New Zealand childhood stroke community.

### Study setting and procedures

The study is being conducted at eight tertiary paediatric hospitals in Australia and one tertiary paediatric hospital in New Zealand that meet recommended international criteria for primary paediatric stroke centres^28^ from 2020 until 2026. These hospitals include (1) the Royal Children’s (RCH) and (2) the Monash Children’s Hospital (MCH), both in Melbourne, Victoria, Australia, (3) the Sydney Children’s Hospital (SCH), (4) the Children’s Hospital at Westmead (CHW), both in Sydney and (5) the John Hunter Children’s Hospital (JHCH), Newcastle, New South Wales, Australia, (6) the Queensland Children’s Hospital (QCH), Brisbane, Queensland, Australia, (7) the Women’s and Children’s Hospital (WCH), Adelaide, South Australia, (8) the Perth Children’s Hospital (PCH), Perth, Western Australia and (9) the Starship Children’s Hospital (StCH), Te Toka Tumai, Auckland, New Zealand (online supplemental e-Table 1).

The Code Stroke protocols tailored to local resources are being primarily followed in the EDs but also target inpatients with conditions associated with a risk of stroke (eg, children with cardiac disease). The EDs are members of the PREDICT research network.^33^ These hospitals will partner with adult comprehensive stroke centres to develop PACS protocols tailored to each hospital. Common elements will include (1) clinical criteria that trigger activation of the Code Stroke protocol, (2) clinical assessment which includes the pedNIHSS, (3) baseline bloods, (4) agreed on minimum imaging dataset (for MRI axial T1, T2, FLAIR, diffusion weighted imaging, apparent diffusion coefficient, susceptibility weighted imaging and time of flight MR angiography sequences and inclusion of CT angiography in CT based protocols) and (5) eligibility for thrombolysis. These elements align with the national childhood stroke guideline. There will be resource-related protocol variability in (1) type of initial imaging (CT vs MRI), (2) use of perfusion imaging and (3) ECR (case-by-case discussion for children presenting in the 6–24 hours’ time-window, and (4) whether this is performed on site at the paediatric hospital or at an adult comprehensive stroke centre.

### Study participants, inclusion and exclusion criteria

During the pre-implementation phase, from 2015 to 2017, children aged 1 month to 18 years with radiologically confirmed stroke will be retrospectively identified from ICD10 principal diagnosis codes for stroke and then medical record review.

During the Code Stroke protocol development and post implementation phases from 2018 to 2026, children aged 1 month to less than 18 years of age with symptoms of less than 24 hours duration that are suspicious for stroke (also referred to as brain attacks)^34^ will be eligible for recruitment to the PACS study. Symptoms include altered consciousness; focal face arm or leg weakness; dysarthria; dysphagia; sensory disturbance; visual disturbance; limb incoordination/ataxia; visual/sensory neglect; pupillary abnormality; severe headache with associated focal neurology and seizure(s) with associated focal neurology^28^ (figure 1). Patients will be categorised into two final diagnostic groups: stroke or mimics, based on presence or absence of acute ischaemic or haemorrhagic infarction on brain imaging. Stroke will be further sub-categorised into AIS or haemorrhagic stroke (HS) as adjudicated by a paediatric radiologist. Children with acute neurological symptoms that are not relevant for stroke will be excluded from the study.

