## Data collection

### Pre-implementation and pre-protocol development phase

All sites will retrospectively collect data for confirmed strokes by case record review from 2015 to 2017, using the ICD-10 codes: I61.0–I61.6, I61.8, I61.9, I62.9, I63.0–I63.6, I63.8, I63.9, I64.0 and G45, for the primary aim of determining time to diagnosis prior to implementation of Code Stroke protocols across study sites (table 1).^40
41^

**Table 1 T1:** Data to be collected

Variables	Pre-implementation (2015–2017) confirmed stroke	Post implementation phase (2018 onwards) stroke	Post implementation phase (2018 onwards) mimics
Demographics	✓	✓	✓
Prehospital care*	✓	✓	✓
Presenting clinical features	✓	✓	✓
pedNIHSS (baseline, 24 and 48 hours)	✓†	✓	✓‡
EMS call taker and paramedic coded diagnoses*	✓	✓	✓
Sensitivity of ED physician diagnosis		✓	✓
Time to diagnosis§	✓	✓	✓
Timelines of care (pre- and post-arrival)	✓	✓	✓
Length of stay, acute hospital and inpatient rehabilitation	✓	✓	✓¶
Follow-up phone call following ED discharge for mimics to confirm no change in diagnosis		✓	✓
Rates of reperfusion therapy use (t-PA and ECR)	✓	✓	
Reperfusion therapy related serious adverse events	✓	✓	
Neurological outcomes: Outcomes: (PSOM and mRS) at discharge 7, 30 and 90 days. mRS at 30 and 90 days	✓	✓	
Child Health Utility (CHU-9D)		✓	
Costs of childhood stroke, using hospital/Medicare linked services health utilisation cost data		✓	

* For the subgroups of children transported to ED by ambulance.

† Paediatric version National Institutes of Health Stroke Scale (pedNIHSS) and Paediatric Stroke Outcome Measures (PSOM) may be derived retrospectively in some (but not all) patients from clinical assessment notes and should be collected if applicable.

‡ Only at baseline.

§ Time to diagnosis will be collected for all children presenting to the emergency department, regardless of mode of arrival and for inpatients where a Code Stroke is activated.

¶ Only if admitted.

ECR, endovascular clot retrieval; ED, emergency department; EMS, emergency medical services; mRS, modified Rankin score; tPA, tissue plasminogen activator.

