## Sample size and power calculations

We anticipate 326 patients with suspected stroke will be recruited during the protocol development and prospective phases of the study (based on numbers of patients recruited to institutional stroke registries in Victoria and New South Wales). Recent literature suggests that approximately one in three children with stroke symptoms will have a final diagnosis of stroke following imaging.^31
43–45^ Therefore, we anticipate 98 participants with a radiologically confirmed diagnosis of stroke in each study phase. Estimates of pre-implementation time to stroke diagnosis are based on extrapolation of local published data^13^ and audit data provided by three study sites. Estimates of post implementation time to stroke diagnosis are based on audit data from Queensland Children’s Hospital, where the proportion of children diagnosed within 4.5 hours increased from 15% to 40% during the 12-month period following introduction of their institutional PACS in 2019. We estimate that 15% of children will be diagnosed within 4.5 hours in the pre-implementation phase, increasing to 40% in the post implementation phase.

The *primary outcome* is the change in the proportion of children with stroke diagnosed within a 4.5-hour time window for reperfusion therapies, pre- and post-PACS implementation (figure 4). Time to diagnosis will be based on radiological confirmation of ischaemic infarction or haemorrhage on CT or MRI. This will be determined by calculating the time elapsed from last seen well to completion of neuroimaging, which is electronically recorded on imaging studies.

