**Figure 4 F4:**
[figure not shown]
PACS study outcome measures and analyses. AIS, arterial ischaemic stroke; AuSCR, Australian Clinical Stroke Registry; BASICS, Brain Attack and Stroke in Children Screen; ED, emergency department; EMS, emergency medical services; PACS, Paediatric Acute Code Stroke; ROC, receiver operating characteristic; tPa, tissue plasminogen activator.

Due to the hospital-based nature of the proposed intervention, when powering this study, we have taken appropriate care of the hierarchical nature of the data, where individual patients are clustered within the treating hospitals. It is therefore appropriate to anticipate the presence of a design effect (expressed through the value of the intraclass correlation coefficient), as would have to be done in the situation of cluster-randomised studies. In addition, different hospitals will be able to recruit different numbers of patients, thus there will be a variation of cluster sizes.

Nine hospitals are participating in the study. At the time of receiving grant funding in July 2020, seven hospitals had agreed to participate in the study. Based on this consideration, assuming the settings of alpha=0.05, the intraclass correlation coefficient of 0.05 (corresponding to a small-to-medium hospital-specific effect) and the coefficient of variation of hospital-based cluster sizes of 0.5 (medium-to-high level of variation) with at least seven hospitals, recruiting the 98 patients with radiologically confirmed diagnosis of stroke in the pre-PACS implementation phase and 98 patients in the post-PACS protocol implementation stage (on average 14 patients per hospital for both pre-implementation and post implementation stages), will yield 80% power to detect a change from 0.15 to 0.40 in proportion of children diagnosed within 4.5 hours of symptom onset.

In addition, this sample size will be sufficient for further validation and continuous updating of the BASICS tool in order to further improve its predictive capacity (as the total number of screened patients is expected to be at least three times the number of confirmed strokes).^30
31^

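### The under-24-hour symptom limit is set for the 2018-2026 cohort only, so the primary before-after comparison favours the post phase whenever any strokes present at 24 hours or later

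*Protocol article*

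**What the plan says.** The section on study participants gives two eligibility rules. For 2015-2017, "children aged 1 month to 18 years with radiologically confirmed stroke will be retrospectively identified from ICD10 principal diagnosis codes for stroke", followed by record review; no limit on symptom duration is stated. The data-collection section for the pre-implementation phase repeats this: "All sites will retrospectively collect data for confirmed strokes by case record review from 2015 to 2017". For protocol development and post implementation, 2018 to 2026, eligibility is for "children aged 1 month to less than 18 years of age with symptoms of less than 24 hours duration that are suspicious for stroke".

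The primary outcome is the change between phases in the proportion of children with stroke diagnosed within 4.5 hours. The section on sample size defines time to diagnosis by "calculating the time elapsed from last seen well to completion of neuroimaging". The data analysis plan estimates the change with a mixed-effects logistic model that has phase as the fixed effect and hospital as the random effect, and no other term.

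The Introduction says that children miss reperfusion treatment "often because of diagnostic delay, sometimes extending beyond 24 hours". The Discussion lists bias from mixing retrospective and prospective collection as a limitation, without mentioning the different eligibility rules.

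**The concern.** The two phases are meant to differ in the presence of Code Stroke. As written, they also differ in which strokes can enter the denominator. Late presenters, who are near-certain failures on a 4.5-hour outcome, are counted before implementation and excluded afterwards. That alone raises the post-phase proportion. Because the limit coincides exactly with phase, it goes into the phase coefficient, and a hospital random effect cannot separate it out. A positive primary result could then be partly a product of eligibility.

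**Working it through.** **Inputs from the protocol article (sample size section).** Rates: "We estimate that 15% of children will be diagnosed within 4.5 hours in the pre-implementation phase, increasing to 40% in the post implementation phase". Clustering: "assuming the settings of alpha=0.05, the intraclass correlation coefficient of 0.05", cluster-size coefficient of variation 0.5, seven hospitals, 14 patients per hospital per phase (98 per phase). Sidedness is not stated; two-sided is assumed here.

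**Input not in the documents.** f, the share of confirmed strokes first presenting at 24 hours or later. It is varied from 0.1 to 0.5.

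**Step 1: the plan's own power.**
- Design effect = 1 + [(1 + 0.5²) × 14 - 1] × 0.05 = 1 + 16.5 × 0.05 = 1.825.
- Effective n per phase = 98/1.825 = 53.7.
- Standard error (unpooled) = √[(0.15 × 0.85 + 0.40 × 0.60)/53.7] = 0.0827, so 0.25/0.0827 = 3.02.
- A cluster t-test with 2 × (7 - 1) = 12 degrees of freedom gives 79.2% power, in line with the stated 80%. The normal formula with pooled null variance gives 83.7%.

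The sample size is therefore reproducible and is not in dispute.

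**Step 2: what the asymmetry does with no intervention effect.** Among N strokes, 0.15N succeed. Symptom duration is read as duration at presentation, so a child presenting at 24 hours or later is not a success. Removing those fN children leaves 0.15N successes among (1 - f)N children, and the post-phase proportion becomes 0.15/(1 - f).

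**Step 3: chance of a falsely significant rise.** With p1 = 0.15, p2 = 0.15/(1 - f), p̄ their mean, n = 53.7 and Φ the standard normal distribution function:

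Φ{[(p2 - p1) - 1.96 √(2p̄(1 - p̄)/n)] / √[(p1(1 - p1) + p2(1 - p2))/n]}

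For f = 0.3, p2 = 0.2143, the difference is 0.0643, the null standard error 0.0745 and the alternative standard error 0.0742. The result is Φ(-1.10) = 0.136.

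| Assumed f | Post proportion, no effect | Spurious rise (points) | Share of planned 25 points | Odds ratio | Falsely significant rise |
|---|---|---|---|---|---|
| 0.1 | 16.7% | 1.7 | 7% | 1.13 | 4% |
| 0.2 | 18.8% | 3.8 | 15% | 1.31 | 7.5% |
| 0.3 | 21.4% | 6.4 | 26% | 1.55 | 14% |
| 0.4 | 25.0% | 10.0 | 40% | 1.89 | 25% |
| 0.5 | 30.0% | 15.0 | 60% | 2.43 | 46% |

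The nominal chance in that direction is 2.5%. With one common limit in both phases, the expected difference under no effect is zero for every f.

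**The case against.** **The size is unknown, and the Introduction does not supply it.** It speaks of delay to diagnosis, not of late arrival. A child who arrives at 3 hours and is imaged at 30 hours is eligible in both phases. The Introduction also ranks in-hospital factors above prehospital ones as causes of delay. This stands: the documents show neither that f is large nor what it is, and the bias is conditional on f above zero.

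**Failure is not strictly certain.** The Discussion notes that about half of children with stroke first present to non-tertiary paediatric hospitals. A child imaged elsewhere within 4.5 hours who reaches a study hospital after 24 hours could count as a success. This stands as a rare exception and does not alter the direction.

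**A reader might infer from accrual that f is large**, since 98 strokes in three pre-phase years compare with 98 over a much longer post phase. The documents do not support this. The figure of 98 is a planning target (14 × 7 hospitals), not an observed count. Slower post-phase accrual also has other possible explanations in the article: pandemic delay, staggered site approvals and prospective consent.

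**A reader might also infer a loss of power**, taking the 15% as an all-comer rate and the 40% as a restricted one. The article attributes the rates to published and audit data without saying which population they describe. If both come from the same all-comer population, a common limit scales both. At f = 0.3 they become 0.15/0.7 = 21.4% and 0.40/0.7 = 57.1%. The normal formula then gives about 98% power at effective n 53.7, or about 90% if that effective n falls by 30% in both phases. The direction of any power change cannot be determined.

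**The limitation is acknowledged, and an unseen analysis plan might apply a common limit.** The acknowledgement is general and corrects nothing. The point rests on two eligibility rules that the article itself states and that differ.

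**Conclusion.** The point holds in conditional form. As written, the plan excludes near-certain failures from the post-phase denominator only and attributes the resulting difference to Code Stroke. The direction follows from the stated eligibility rules and outcome definition for any f above zero. The size does not: over assumed f of 0.1 to 0.5 the spurious rise is 1.7 to 15 points, and the chance of a falsely significant result in favour of Code Stroke is about 4% to 46%. These figures assume a true rate of 15% in both phases among all strokes, a two-sided 5% test, the plan's design effect, and 98 analysed strokes per phase. Because the primary estimate is affected in the favourable direction, this should be settled before the analysis. The differing upper age wording (to 18 against under 18 years) is minor and can be aligned in the same edit.

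**What to change.** 1. Derive symptom duration at first presentation for the 2015-2017 cases from the pre- and post-arrival timelines that Table 1 already collects.
2. Restrict the primary analysis set to symptoms under 24 hours and age under 18 years in both phases.
3. Report the comparison with the unrestricted pre-phase cohort as a sensitivity analysis, and report the number of pre-phase cases that the restriction removes, which gives f directly.
4. Check whether the 15% and 40% planning rates and the 98 pre-phase cases refer to this common population. If they do not, restate the power.

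The cost is a change of wording and a filter on data already being abstracted, plus fewer pre-phase cases in the primary set. No new case search for 2018-2026 is needed.
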